## Methods/Design

A quasi-experimental design based on comparison of two non-randomized groups was chosen to assess the effectiveness of the multidisciplinary, multicenter COPD PROCESS management model. The intervention group will consist of all patients with COPD in the area served by Hospital de la Santa Creu i Sant Pau in Barcelona. The control group will comprise all COPD patients in the area served by Hospital de la Vall d'Hebron, also in Barcelona. Randomization was not feasible because only health-care professionals within the intervention area can undertake the coordinated care protocols necessary for implementing the PROCESS protocol. The study will include pre- and post-intervention assessment after 18 months (Figure 1). This project and the study were presented to and approved by the Clinical Research Ethics Committee of Hospital de la Santa Creu i Sant Pau.

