	**491.8 Other chronic bronchitis**	
	**496 Chronic airway obstruction, not elsewhere classified**	

ICD = International Classification of Diseases, with modifications approved by the World Health Organization

ICPC = International Classification of Primary Care (WONCA – World Organization of Family Doctors)

Additionally, a cohort will be selected in order to analyze the clinical and health-care variables. These patients must also meet the following additional inclusion criteria: 1) be able to perform spirometry; 2) meet spirometry criteria for a diagnosis of COPD: lung disease characterized by irreversible airflow limitation defined by a ratio of forced expiratory volume in 1 second [FEV_1_] to forced vital capacity ≤70% after a negative bronchodilator test, and in case of a positive postbronchodilator test (an increase in FEV_1 _of >12% and >200 mL after the use of 400 μg of salbutamol) not having a personal history of asthma, symptoms of atopy or a smoking habit of <40 pack-years. Additional exclusion criteria for this cohort were 1) a diagnosis of any terminal disease that indicates a survival prognosis <6 months, 4) advanced heart failure, 5) sequelae of pulmonary tuberculosis, and 6) lung cancer. All patients will have to give their written, informed consent to be enrolled.

Patients with other respiratory or nonrespiratory diseases can be included in the study provided they do not interfere with measurements. The testing of patients in a period of COPD exacerbation will generally be postponed until the disease has been stable for at least one month. Patients with exacerbated disease will not be excluded from the study, however; in case of continuously recurring exacerbations, the patient will be tested in that clinical state.

Calculation of the cohort size: For two-tailed comparisons, accepting an alpha risk of 0.05 and a beta risk of 0.2, to detect a statistically significant between-group CRQ score increment of 0.5 points (the minimum clinically significant difference) [38], and assuming a homogeneous standard deviation of 1.7 and a loss to follow-up of 10%, we have calculated that 220 patients will be required in each cohort. A simple random sampling procedure will be used to select the cohort patients.

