### Study variables

Table 2 shows the variables measured for the study [43-46]. Two complementary dimensions of the PROCESS model will be measured. One involves health-care management. To assess that dimension, clinical and administrative data for the entire population will be extracted from the records of the participating centers. The inclusion of this dimension addresses the issue of the impact on the health-care system (objective 1). The second, clinical dimension will be evaluated on the basis of data from the intervention and control cohorts. For that purpose, data will come from both medical records and visits with patients. The assessment of this dimension corresponds to the evaluation of patient health and quality-of-life benefits (objective 2).

**Table 2 T2:** Study variables for the evaluation of the COPD PROCESS

**Group**	**Variables**
Social and demographic characteristics:^†‡^	Primary care clinic assignment; date of birth; sex.
Patient and lung function characteristics:^‡^	Weight; height; spirometry performed in the past year.
	Spirometry results after bronchodilator (Datospir 120, model A, SIBEL, S.A, Barcelona, Spain; after calibration, with daily maintenance by expert nurses, and quality assurance).
	Carbon monoxide in expired air; pulse oximetry; COPD stage (GOLD criteria); year COPD was diagnosed.
Clinical status (last 6 months):^†‡^	Smoking (frequency, pack-years, cessation phase, enrollment in a cessation program, adherence to recommended preventive measures); exercise (type of activity, duration in minutes and days per week); adherence to any medical advice that has been given; Charlson comorbidity index [43]; dyspnea severity (Medical Research Council Breathlessness scale [44]).
Medication:^‡^	Active principle and pharmaceutical class, dosage.
	Inhalers: number of inhaler devices used in the last month, level of handling expertise (correct performance of 3 actions for a specific inhaler type).
	Oral medications (glucocorticosteroids, theophylline, antioxidants) and their agreement between the patient's report and the medical record.
	Supplemental oxygen therapy; mechanical ventilation; annual vaccination or in the previous winter (flu, pneumococcus)
	Attendance at COPD management training sessions or specific sessions related to medication type.
	Deviations from the PROCESS model (lack of agreement between drugs taken and those recommended for the recorded GOLD severity stage).

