### Statistical analysis

Patients with COPD in the intervention and control areas will first be described using parameters of point estimation and their 95% confidence intervals. The groups will then be compared based on bivariate hypotheses on pre- to post-intervention changes in process and outcome variables. The statistical tests that will be used will depend on the nature of the variable studied.

Analysis of the health-care dimension will focus on the impact of the COPD PROCESS model within the health-care delivery system (objective 1), based on comparing the utilization of resources and visits to primary and specialist care facilities in the intervention and control areas. The principal outcome measure will be the change in annual rate of scheduled and unscheduled admissions that are made with a main diagnostic code of COPD (Table 1) or another code related to a respiratory system process. The year prior to implementation of the PROCESS management system will be compared to the last 12 months of implementation. The difference between the rates of the two study areas will be estimated using the indirect standardization method in which the population assigned to each health-care area will be used as the standard. If possible, a more precise analysis of the differences in rates will be undertaken by constructing linear multiple regression models adjusted for the distribution of the dependent variable (negative binomial, Poisson, beta), a procedure which corrects for confounding factors.

For the clinical dimension, health status and quality of life will be compared between patients in the intervention and control areas (objective 2). The main outcome measure will be minimal clinically significant differences between pre- and post-intervention quality-of-life scores. A test of comparison between two independent means will be used for comparisons with the control group. If multivariate analysis is necessary, multiple regression models will be constructed.

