### Strengths and possible limitations of the study

The limitations inherent to any evaluative or quasi-experimental study are also present in this research. Patients cannot be randomized for this study. Nonetheless, the design is the most robust one available and will provide the strongest evidence possible, within the existing constraints. Possible differences that might emerge between the control and intervention groups will be adjusted by applying multiple regression analysis.

The use of clinical and administrative databases as sources of information places limitations on the comprehensiveness of the analysis and its validity, as the quality of data is dependent on the information storage interface and its adequate and proper use by health-care professionals. It was expressly decided, however, not to create dedicated databases given that the pragmatic nature of the model requires that the information sources be integrated into the daily work routines of the physicians and nurses who are caring for the patients. The inclusion of the study cohorts will counterbalance this limitation.

Implementing a multidisciplinary model over such an extensive geographic area and working with such a large number of clinical caregivers is a complex undertaking. Adequate and consistent adherence to the PROCESS protocols at all the health-care facilities will require a very high level of dedication. Therefore, it will be essential to integrate the project-specific software into the records of the care facilities. Periodic meetings to coordinate and supervise the participants will also be required.

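### Covariate adjustment of the main quality-of-life comparison is left conditional on the data, although the two areas are not randomized

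*Protocol article*

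**What the plan says.** The Methods/Design section describes the allocation plainly: "A quasi-experimental design based on comparison of two non-randomized groups was chosen". Under Setting, the intervention area has 10 centers run by the Catalan Health Institute and 7 run by other kinds of provider; all 17 control centers belong to the Institute.

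The Statistical analysis section opens with a general approach: "The groups will then be compared based on bivariate hypotheses on pre- to post-intervention changes in process and outcome variables". For the clinical dimension (objective 2) it then gives three statements in sequence:

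- outcome: "The main outcome measure will be minimal clinically significant differences between pre- and post-intervention quality-of-life scores"
- test: "A test of comparison between two independent means will be used for comparisons with the control group"
- adjustment: "If multivariate analysis is necessary, multiple regression models will be constructed"

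The Strengths and possible limitations section returns to adjustment: "Possible differences that might emerge between the control and intervention groups will be adjusted by applying multiple regression analysis".

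The cohort-size calculation under Type of participant aims "to detect a statistically significant between-group CRQ score increment of 0.5 points", with a standard deviation of 1.7 and 10% loss, and arrives at 220 per cohort. Table 2 lists, for the cohort patients, date of birth, sex, spirometry, GOLD stage, smoking, and "Charlson comorbidity index [43]; dyspnea severity (Medical Research Council Breathlessness scale [44".

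**The concern.** Quality of life is one of the two principal endpoints. As written, its headline result is a comparison of means without covariates. Whether a regression replaces or accompanies it is decided later, with no stated trigger. The two sections do not give the same rule: one adjusts when this is found necessary, the other when differences emerge. Both call for a look at the data first.

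In a randomized trial this would matter less. Here two health-care areas are compared, and the possibility that their patients differ in age, severity, smoking or comorbidity follows from the design rather than from any baseline test. Such factors can influence how much a patient's CRQ score moves over 18 months. Two analysts following the text faithfully could report an unadjusted or an adjusted difference as the main finding, and the choice could be made after both are known.

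**Working it through.** **The plan's own figure.** Inputs from the cohort-size calculation: difference 0.5, SD 1.7, two-sided alpha 0.05, power 80%.

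- n per group = 2 × (1.960 + 0.842)² × 1.7² / 0.5² = 181.5, so 182.
- With 10% loss: 182 / 0.9 = 202.2, so 203.

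The stated 220 is larger than this and so errs on the safe side. The discrepancy is a separate matter and does not affect the present point. From 220, the evaluable number is 220 × 0.9 = 198 per arm, which gives 83.3% power for a true difference of 0.5.

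**The two adjustment rules side by side.**

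| Section | Adjustment happens when | Criterion | Covariates |
|---|---|---|---|
| Statistical analysis (objective 2) | it is found necessary | none | none named |
| Strengths and possible limitations | differences emerge | none | none named |

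**What a bias in change would do to the unadjusted test.** Assume 1.7 is the SD of change; the article does not say whether it refers to change or to a single score. With equal variances at both visits the two readings coincide at a pre-post correlation of 0.5, because SD of change = 1.7 × √(2 × (1 − 0.5)) = 1.7.

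- SE of the difference in mean change = 1.7 × √(2/198) = 0.171.
- For a shift b unrelated to the program, the rejection rate under a true null is 1 − Φ(1.96 − b/SE) + Φ(−1.96 − b/SE).

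| Assumed shift b (CRQ points) | b / 0.5 target | b / SE | Rejection of a true null |
|---|---|---|---|
| 0 | 0% | 0 | 5.0% |
| 0.1 | 20% | 0.59 | 9.0% |
| 0.2 | 40% | 1.17 | 21.6% |
| 0.3 | 60% | 1.76 | 41.9% |

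The shifts are assumptions; the article gives no figure for them.

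**Whether adjustment can be afforded.** If baseline CRQ is included and variances are equal at both visits, the residual variance relative to that of change is (1 − r²) / (2(1 − r)) = (1 + r)/2. Applied to 181.5 per group:

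| Assumed r | Ratio | n per group | With 10% loss |
|---|---|---|---|
| 0.3 | 0.65 | 118 | 132 |
| 0.5 | 0.75 | 137 | 153 |
| 0.7 | 0.85 | 155 | 173 |
| 0.8 | 0.90 | 164 | 183 |

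All are below 220. Imbalance of the covariates between areas takes back some of this gain, but the planned cohorts leave room for it.

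**The case against.** **The article does provide for adjustment, and detail can wait for the analysis plan.** This stands in part. A covariate list is commonly left to a statistical analysis plan, which is not shown here, and its absence is no fault. What the article does fix is that the main comparison is a two-means test and that adjustment is contingent. A rule that depends on the data, worded in two ways, is a flaw in what is written.

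**The comparison is of changes, so it is not naive.** Correct. A reader might infer that any baseline gap in CRQ passes straight into the effect. It does not: stable differences in level cancel. Nor should a chance gap between the two random samples be called confounding. A gap of 0.3, for instance, would be about 1.76 standard errors (0.3 / 0.171, if the baseline SD is also 1.7), and chance imbalance of this kind is already reflected in the standard error of the change difference. What remains is case-mix effects on change, and differing trends.

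**The outcome looks like a responder status.** A reader might take the outcome sentence to mean the share of patients who improve by at least 0.5, and conclude that endpoint and test contradict each other. On that reading, with normal change and means of 0 and 0.5, the proportions would be 38.4% and 50.0%, and power at 198 per arm about 64% instead of 83%. The documents do not support it. The next sentence names a means test, the sample size rests on a between-group increment of 0.5, and no proportion of improvers is mentioned anywhere. The text reads as mean change with 0.5 as the threshold of relevance; only the wording could be clearer.

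**Adjusting for baseline CRQ is not free of assumptions.** This stands. If the areas differ stably at baseline, the change-score difference is unbiased under parallel trends, while the baseline-adjusted estimate can be off by (1 − r) times the gap. If the areas share the same underlying mean, adjustment is the better choice. Neither dominates in a two-area design, so both belong in the report.

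**Conclusion.** The point holds in this limited form: the main objective 2 analysis is a comparison of mean changes without covariates, and its adjustment is contingent, has no trigger and is worded inconsistently between two sections. In a non-randomized comparison of areas with different provider mix, this can leave case-mix bias in a principal result and leaves the choice of headline estimate open until the data are seen.

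The size is illustrative: a null rejection rate of about 9% to 42% in place of 5%, for assumed shifts of 0.1 to 0.3 CRQ points, 198 evaluable per arm and an SD of change of 1.7. Nothing in the article shows that a shift of this size will occur. Regression on Table 2 covariates removes only the part of a shift that those covariates explain; trends that belong to the area itself would remain. This is something that should be changed, not a defect that invalidates the design.

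**What to change.** In the Statistical analysis section, delete the conditional clause on multivariate analysis. State that the primary objective 2 analysis is a regression of 18-month CRQ change on area, adjusted in every case for baseline CRQ and a fixed set from Table 2: age, sex, GOLD stage or FEV1, smoking, Charlson index and MRC dyspnea. Report two sensitivity analyses: the unadjusted difference in mean change, and the adjusted model without baseline CRQ. Reword the sentence in Strengths and possible limitations so that it states the same unconditional rule.

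As a minor clarification, say that the outcome is the between-area difference in mean CRQ change, with 0.5 points as the threshold for interpretation, as the sample-size paragraph already implies.

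Cost: a change of wording and a little more analysis, with no new variables or patients. The estimates with and without baseline CRQ may differ if the areas differ stably at the start. The report then has to discuss that difference, which is why both are shown.

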## Discussion

The COPD PROCESS evaluation study offers a unique opportunity to learn about the performance of a health management model that is integrated, multidisciplinary, adapted to conditions in Spain and possibly appropriate for countries with similar characteristics. The knowledge gained will be an important contribution given that few full descriptions of such experiences are available in the literature. If we are able to demonstrate the feasibility and benefits of the PROCESS model, a substantial innovation in health-care organization will become available. Objective, scientific evidence of the impact of a model of health-care delivery on COPD in terms of patient health and quality of life will be of great importance and help palliate the considerable morbidity and mortality this disease causes. The result will be a better system in which resources for patient care are handled more rationally and efficiently to deliver higher quality health care.

Although the fact of implementing the model in a local health-care area may suggest that the results cannot be extrapolated to other settings with different characteristics, the intervention area has no singularly differentiating characteristics and the project will require no investment of resources other than those usually available to any similar health-care system. This project therefore has the external validity necessary to generalize the results to at least the Spanish national health-care system and assure that the impact it might have on health and the health-care system will be highly relevant.

### Strengths and possible limitations of the study

The limitations inherent to any evaluative or quasi-experimental study are also present in this research. Patients cannot be randomized for this study. Nonetheless, the design is the most robust one available and will provide the strongest evidence possible, within the existing constraints. Possible differences that might emerge between the control and intervention groups will be adjusted by applying multiple regression analysis.

The use of clinical and administrative databases as sources of information places limitations on the comprehensiveness of the analysis and its validity, as the quality of data is dependent on the information storage interface and its adequate and proper use by health-care professionals. It was expressly decided, however, not to create dedicated databases given that the pragmatic nature of the model requires that the information sources be integrated into the daily work routines of the physicians and nurses who are caring for the patients. The inclusion of the study cohorts will counterbalance this limitation.

Implementing a multidisciplinary model over such an extensive geographic area and working with such a large number of clinical caregivers is a complex undertaking. Adequate and consistent adherence to the PROCESS protocols at all the health-care facilities will require a very high level of dedication. Therefore, it will be essential to integrate the project-specific software into the records of the care facilities. Periodic meetings to coordinate and supervise the participants will also be required.

## Abbreviations

COPD: Chronic Obstructive Pulmonary Disease; FEV_1_: Forced expiratory volume in 1 second; GOLD: Global Initiative for Chronic Obstructive Lung Disease; ICD: International Classification of Diseases, with modifications approved by the World Health Organization; ICPC: International Classification of Primary Care; WONCA: World Organization of Family Doctors; UFISS: Social and Health Care Interdisciplinary Functional Unit for geriatric patients of the hospital; PADES: Home Care and Support Teams.
